**post-operative endpoints (one month after discharge)**

　　　Interview and examine the patient for the development of analgesia-related adverse events at the time of the outpatient visit.

　　　If it is difficult to come to the hospital within one month after surgery, it is acceptable to come to the hospital within three months after surgery.

**adverse events/side effects**

**adverse events**

Any new unfavourable or unintended signs (including abnormal laboratory values), symptoms, diseases or events that occur after the start of the study, whether or not causally related to epidural analgesia and patient-controlled analgesia.

**side effects**

An adverse event is defined as any event that is determined, for some reasonable reason, to be associated with the epidural analgesia or patient-controlled analgesia procedure. In other words, an adverse event is defined as any medically determined adverse event that occurs in a subject because of the epidural analgesia or patient-controlled analgesia procedure. Generally, an association with epidural analgesia or patient self-administered analgesia is assessed as 'yes' when the rationale or reason for the association can be identified.

**serious adverse events or serious side effects**

Among adverse events, serious adverse events are defined as the following.

(i) Deceased.

(ii) Of life-threatening substances.

(iii) Those requiring hospitalisation or an extended period of hospitalisation for treatment.

(iv) Permanent or marked impairment or dysfunction.

(v) those with congenital diseases or anomalies in later generations.

**recording and assessment of adverse events**

For adverse events, the following criteria are used to assess severity and causal relationship to epidural analgesia or patient-controlled analgesia. The severity and causal relationship assessment will be determined in consultation with the Effectiveness and Safety Assessment Committee*.

　　　*The Effectiveness and Safety Assessment Committee shall consist of the following three members.

　　　　Assistant [name], Department of Gastrointestinal Surgery, Okayama University Hospital

　　　 Assistant [name], Department of Hepatobiliary and Pancreatic Surgery, Okayama University Hospital

　　　　Third-party position Assistant [name], Center for Innovative Clinical Medicine, Okayama University Hospital

**severity assessment**

Evaluate the severity of adverse events/side effects according to CTCAE v4.0.

**causality assessment**

[Clearly relevant] : clearly related to epidural analgesia or patient self-administered analgesia from a clinical/biological point of view. In this case, treat as a side effect.

[Probably related]: strongly suspected to be related to epidural analgesia or patient self-administered analgesia from a clinical/biological point of view and for which a reasonable explanation is possible, such as time course from epidural analgesia or patient self-administered analgesia use to the occurrence of the adverse event or its disappearance after discontinuation of use. In such cases, treat as an adverse effect.

[Likely association]: suspected association with epidural analgesia or patient self-administered analgesia from a clinical/biological point of view, based on the time course from the start of epidural analgesia or patient self-administered analgesia use to the occurrence of the adverse event. In this case, treat as an adverse effect.

[Probably not related]: when an association with epidural analgesia or patient self-administered analgesia can be ruled out and other causes are indicated. In this case, treat as an adverse event.

[Obviously not related]: when an association with epidural analgesia or patient self-administered analgesia can be clearly ruled out and a link to other causes is strongly considered. In this case, treat as an adverse event.

**4. Evaluation items**

　　　● Primary endpoint

　　　　　　Pain score using Numerical Rating Scale (NRS) at rest 24 hours after surgery.

　　 ● Secondary endpoints

　　　　　　Days to achieve discharge criteria*, Duration of postoperative hospital stay, Incidence of postoperative complications, Pain score (NRS) on postoperative days 2, 3 and 4 at rest, Additional analgesic usage, Analgesic method-related complications.

*Discharge criteria: (1) Good pain control with oral analgesics (2) Able to walk on own (3) Consume more than half of meal (4) No post-operative complications, or as far as possible treated on an outpatient basis.

**5. Data aggregation and statistical analysis methods**

**data aggregation**

　　　The types of reports to be submitted are listed below, and the Secretariat will enter information on the submitted reports into a database.

　　　Case registration form ............................. Submitted to the Secretariat at the time of registration.

　　　Case record form (pre-surgery) .................... Submitted to the office before surgery.

　　　Case record form (during hospitalisation) .................... Submitted to the secretariat as soon as possible after discharge from hospital.

　　　Adverse event report form ........................... Submitted to the Secretariat as soon as possible upon occurrence of an adverse event.

**statistical analysis methods**

　　　After enrolment in the study, patients who did not withdraw their consent and for whom protocol treatment was administered will be included in the analysis population (Full analysis set, FAS). For the analysis of the primary endpoint, NRS at 24hrs after surgery of the EDA and iv-PCA groups will be calculated for the FAS and analysed by Student t-test. Secondary endpoints will be analysed by the X^2^ test was employed to analyze categorical variables. Welch’s t test was used to compare continuous variables.

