**0. Overview.**

**0.1. objectives**

　To test the non-inferiority of intravenous patient-controlled analgesia (iv-PCA) as postoperative analgesia to epidural analgesia (EDA) with respect to post-operative analgesia in patients aged 20 years and older undergoing laparoscopic gastrectomy for gastric cancer.

● Primary endpoint

　　　　　　Pain score using Numerical Rating Scale (NRS) at rest 24 hours after surgery.

　　● Secondary endpoints

　　　　　　Days to achieve discharge criteria*, Duration of postoperative hospital stay, Incidence of postoperative complications, Pain score (NRS) on postoperative days 2, 3 and 4 at rest, Additional analgesic usage, Analgesic method-related complications.

*Discharge criteria: (1) Good pain control with oral analgesics (2) Able to walk on own (3) Consume more than half of meal (4) No post-operative complications, or as far as possible treated on an outpatient basis.

● Safety assessment.

　　　　　　Frequency of analgesia-related adverse events.

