**6. Target case numbers and rationale for setting them**

[Target number of cases] 132 cases

[Rationale for setting up the case number].

In a retrospective study of patients who underwent laparoscopic gastrectomy for gastric cancer at our hospital and who received postoperative pain management with EDA or iv-PCA, respectively, the mean 24-hour postoperative pain score (NRS) was 2.11 and standard deviation 1.9 in the EDA group, and in the iv-PCA group the mean 2.36 with a standard deviation of 1.8.

Since only patients who meet the inclusion criteria and do not meet the exclusion criteria will be included in this study, it is assumed that the variation in scores will be smaller than in the existing data, as the patients will be more similar than in the existing data. Therefore, in the caseload design of this study, it is assumed that the standard deviation will be about 10% smaller, with a mean of 2.11 and a standard deviation of 1.71 for the EDA group and a mean of 2.36 and a standard deviation of 1.62 for the iv-PCA group.

Assuming a non-inferiority margin of 1 and a sample size of α = 0.05 and β = 0.2, the sample size is 62 cases in one group (124 cases in both groups). Assuming a drop-out rate of approximately 5%, the target number of cases is 132 in both groups.

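### The primary analysis is named only as a Student t-test; the margin of 1 is not carried into it, so as written it does not deliver the non-inferiority conclusion

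*Protocol*

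**What the plan says.** Section 0.1 of the protocol gives the objective: "To test the non-inferiority of intravenous patient-controlled analgesia (iv-PCA) as postoperative analgesia to epidural analgesia (EDA"). The primary endpoint in section 4 is "Pain score using Numerical Rating Scale (NRS) at rest 24 hours after surgery", where lower is better.

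Section 6 builds the sample size on non-inferiority: "Assuming a non-inferiority margin of 1 and a sample size of α = 0.05 and β = 0.2". For the control arm it assumes scores "with a mean of 2.11 and a standard deviation of 1.71 for the EDA group". The corresponding assumption for the experimental arm is "a mean of 2.36 and a standard deviation of 1.62 for the iv-PCA group". The result is 62 per group, raised to 132 in total for about 5% drop-out. Section 6 does not say whether α is one-sided or two-sided.

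Section 5, under statistical analysis methods, gives the whole primary analysis in one sentence: "NRS at 24hrs after surgery of the EDA and iv-PCA groups will be calculated for the FAS and analysed by Student t-test". It states no null hypothesis, margin, confidence interval, sidedness or criterion for success. The margin appears only in section 6.

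**The concern.** Without qualification, a Student t-test comparing two groups is read as a test of zero difference. That is a different question from whether iv-PCA is worse than EDA by less than 1 point. Failure to reject equality does not show that the excess lies below the margin. The same part of section 5 goes on to assign Welch's test to secondary continuous variables, and nothing in the wording marks the primary test as a margin test.

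At stake is the trial's one confirmatory claim. As the text stands, its criterion and its error level could be settled after the data are seen. An analyst who follows section 5 literally would produce a p-value that neither establishes nor rules out non-inferiority as the objective defines it.

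**Working it through.** **Inputs (section 6).** Margin 1; means 2.11 (EDA) and 2.36 (iv-PCA), so the assumed true excess is 0.25; SDs 1.71 and 1.62; α = 0.05, β = 0.2. The retrospective SDs are 1.9 and 1.8. Group sizes are 62 (before drop-out) and 66 (target).

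**1. Reproduce the plan's figure.** Pooled SD = √((1.71² + 1.62²)/2) = 1.666. The distance from the assumed truth to the margin is 1 − 0.25 = 0.75.

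Normal approximation: n = 2 × ((z₁₋α + z₀.₈) × 1.666 / 0.75)².
- One-sided 0.05: 2 × ((1.645 + 0.842) × 1.666 / 0.75)² = 61.0, so 61. The noncentral t gives 62, with power 80.2%. This matches.
- One-sided 0.025: 78 (79 with the noncentral t). This does not match.
- A true difference of 0 gives 35 (one-sided 0.05) or 44 (one-sided 0.025). Neither matches.

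Drop-out: 62 / 0.95 = 65.3, so 66 per group and 132 in total. This matches.

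The 62 is therefore a margin-based calculation at one-sided 5%.

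**2. Compare the two criteria on the planned SDs.** SE = 1.666 × √(2/n).

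| Per group | SE | Equality test gives p > 0.05 if excess is below | Margin met at one-sided 5% if excess is below | Margin met at one-sided 2.5% if excess is below |
|---|---|---|---|---|
| 62 | 0.299 | 1.980 × 0.299 = 0.592 | 1 − 1.657 × 0.299 = 0.504 | 1 − 0.592 = 0.408 |
| 66 | 0.290 | 1.978 × 0.290 = 0.574 | 1 − 1.657 × 0.290 = 0.520 | 1 − 0.574 = 0.426 |

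At 66 per group, an observed iv-PCA excess between 0.520 and 0.574 is not significant on the equality test and yet fails the margin test at one-sided 5%. At one-sided 2.5% the zone runs from 0.426 to 0.574.

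**3. Hypothetical error rate if p > 0.05 were taken as non-inferior.** At a true excess of exactly 1.0, the false-claim rate is P(|T| < t₀.₉₇₅), where T is noncentral t with noncentrality 1/SE and 2n − 2 degrees of freedom.

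| SDs | 62 per group | 66 per group |
|---|---|---|
| 1.71 / 1.62 (planned) | 8.7% | 7.2% |
| 1.9 / 1.8 (retrospective) | 15.3% | 13.1% |

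A margin test holds its nominal level, 5% by design, in all four cells. Under the equality reading the error rises as the data get noisier or the groups smaller.

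**4. Power of the margin test at an excess of 0.25, planned SDs.**

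| One-sided α | 62 per group | 66 per group |
|---|---|---|
| 0.05 | 80.2% | 82.3% |
| 0.025 | 70.1% | 72.8% |

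**The case against.** The best reply is that section 5 never states its null. A t-test of H0: difference ≥ 1, or the matching confidence limit, is also a Student t-test. The objective, the margin and the reproduced 62 per group all suggest that the authors had such a test in mind. Details of intervals and sidedness are also often left to a statistical analysis plan, which may exist but is not shown.

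Much of this stands. A reader might infer that the protocol commits to an equality test and so cannot answer its question. The text does not go that far: equality is the default reading of an unqualified t-test, not a stated hypothesis. A reader might also infer that the trial will declare non-inferiority from p > 0.05. No section says so, and the rates in step 3 apply only if someone adopts that rule. Nor should one expect a significant iv-PCA excess to sit alongside non-inferiority here. At the planned SE every significant excess (above 0.592 at 62 per group) also fails the margin (0.504). The two could coexist at one-sided 5% only if the SE fell below about 0.275.

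What does not stand is the appeal to a later plan. The protocol itself fixes the primary test and omits the margin from it. An analysis plan that copies the sentence inherits the gap, and one that supplies a margin test adds a criterion the protocol's analysis section does not contain.

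**Conclusion.** The point holds as a mismatch between the analysis section and both the objective and the sample size basis. The named test, as written, does not deliver a non-inferiority conclusion, and nothing elsewhere in the protocol supplies a decision rule.

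Its numerical size is conditional. If non-significance were read as non-inferiority, the false-claim rate at the margin would be 7.2% at the target size with planned SDs and 13.1% with the retrospective SDs, instead of 5%. These figures assume normal-theory t-tests with a pooled variance, two-sided 5% for the equality test, and full data at the stated group sizes. That α is one-sided is inferred from reproducing 62; section 6 does not say it. The point matters because it concerns the criterion for the only confirmatory claim.

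**What to change.** Replace the primary-analysis sentence in section 5 with:

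> The difference in mean 24 h NRS at rest (iv-PCA minus EDA) will be estimated in the FAS with a two-sided 90% confidence interval from the t distribution. Non-inferiority is concluded if the upper limit is below 1.0 (H0: difference ≥ 1.0, one-sided α = 0.05). No conclusion on non-inferiority is drawn from a test of equality.

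In section 6, state that α = 0.05 is one-sided. Of the one-sided levels checked (0.05 and 0.025), it is the only one that reproduces 62 per group.

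If the sponsor prefers a 95% interval (one-sided 0.025), restate the power as about 70% at 62 per group (73% at 66); 80% would need about 78 to 79 per group before drop-out.

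The cost is one paragraph in section 5 and a few words in section 6. At one-sided 5% it needs no new data and no additional patients.

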**6. Target case numbers and rationale for setting them**

[Target number of cases] 132 cases

[Rationale for setting up the case number].

In a retrospective study of patients who underwent laparoscopic gastrectomy for gastric cancer at our hospital and who received postoperative pain management with EDA or iv-PCA, respectively, the mean 24-hour postoperative pain score (NRS) was 2.11 and standard deviation 1.9 in the EDA group, and in the iv-PCA group the mean 2.36 with a standard deviation of 1.8.

Since only patients who meet the inclusion criteria and do not meet the exclusion criteria will be included in this study, it is assumed that the variation in scores will be smaller than in the existing data, as the patients will be more similar than in the existing data. Therefore, in the caseload design of this study, it is assumed that the standard deviation will be about 10% smaller, with a mean of 2.11 and a standard deviation of 1.71 for the EDA group and a mean of 2.36 and a standard deviation of 1.62 for the iv-PCA group.

Assuming a non-inferiority margin of 1 and a sample size of α = 0.05 and β = 0.2, the sample size is 62 cases in one group (124 cases in both groups). Assuming a drop-out rate of approximately 5%, the target number of cases is 132 in both groups.

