**Inclusion criteria**

1) Patients with gastric cancer which has been diagnosed histologically and scheduled to undergo laparoscopic gastrectomy (total gastrectomy, distal gastrectomy or proximal gastrectomy).

　　　2) Patients aged between 20 and 80 years

　　　3) Patients who can provide written informed consent

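### The 80% power in section 6 rests on a 10% cut in the observed SDs that has a stated reason but no data for its size; at the observed SDs it is about 73%

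*Protocol*

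**What the plan says.** Section 6 of the Protocol takes its planning values from a retrospective series of patients at the same hospital who had laparoscopic gastrectomy with EDA or iv-PCA. In that series the mean score "was 2.11 and standard deviation 1.9 in the EDA group"; the corresponding figures under iv-PCA were 2.36 and 1.8.

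The section then expects less variation in the trial, "as the patients will be more similar than in the existing data", because only patients meeting the eligibility criteria enter. On that basis "it is assumed that the standard deviation will be about 10% smaller". The calculation therefore uses SDs of 1.71 for EDA and 1.62 for iv-PCA, while the means are carried over.

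With a margin of 1, α = 0.05 (sidedness not stated) and β = 0.2, the section arrives at 62 per group, and at 132 in total after allowing for about 5% drop-out. Section 5 (statistical analysis methods) analyses the primary endpoint by an unadjusted Student t-test. Section 2 (case registration and allocation methods) describes a stratified block allocation but does not name the strata.

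**The concern.** The observed SDs are the only variability data in the document, and they come from the same hospital, operation and analgesic methods. A 10% lower SD is a 19% lower variance (0.9² = 0.81). The section gives a qualitative argument for some reduction. For its size it gives no SD in the subset of the series that would have been eligible, no source and no sensitivity calculation.

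If the reduction is smaller than assumed, the trial has less power than section 6 says. What is at stake is the chance of an inconclusive result when iv-PCA is in truth only 0.25 points worse. The t-test uses the variance actually observed, so an optimistic planning SD does not raise the false-positive rate.

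**Working it through.** **Inputs, all from section 6:** margin 1; assumed true difference 2.36 − 2.11 = 0.25, so the distance to the margin is 0.75; α = 0.05; power 80%; 62 evaluable per arm, 66 enrolled per arm.

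**Formulas.** Pooled SD s = √((SD₁² + SD₂²)/2). Normal approximation: n per arm = 2·[s·(z₁₋α + z₀.₈)/0.75]². Power from the noncentral t distribution with 2n − 2 degrees of freedom and noncentrality 0.75/(s·√(2/n)).

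**Step 1: reproduce the plan.**
- Cut: 1.9 × 0.9 = 1.71 and 1.8 × 0.9 = 1.62.
- s = √((1.71² + 1.62²)/2) = 1.666.
- One-sided 0.05: n = 2·[1.666 × (1.645 + 0.842)/0.75]² ≈ 61.0, that is 61 by the normal approximation and 62 by the t distribution. This is the plan's figure.
- One-sided 0.025: 78 (normal) or 79 (t). This is not the plan's figure, so the plan was sized at one-sided 5%.
- Drop-out: 62/0.95 = 65.3, rounded up to 66 per arm, 132 in total. Reproduced.
- Power at 62 per arm: 80.2%. The evaluable number is the smallest that reaches 80%, so nothing is held in reserve.

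**Step 2: vary only the SDs** (one-sided 5%, difference 0.25, margin 1, noncentral t).

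| SDs (EDA / iv-PCA) | Pooled SD | Power, 62 per arm | Power, 66 per arm | n per arm for 80% |
| --- | --- | --- | --- | --- |
| 1.71 / 1.62 (full 10% cut) | 1.666 | 80.2% | 82.3% | 62 |
| 1.805 / 1.71 (half the cut) | 1.758 | 76.3% | 78.6% | 69 |
| 1.9 / 1.8 (observed) | 1.851 | 72.5% | 74.9% | 76 |

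The last row in full: s = √((1.9² + 1.8²)/2) = 1.851; standard error at 62 per arm = 1.851 × √(2/62) = 0.332; noncentrality = 0.75/0.332 = 2.26; critical t on 122 degrees of freedom = 1.657; power = 72.5%.

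With half the cut, 80% needs 69 per arm, more than the 66 to be enrolled. The stated power is then missed even if nobody drops out.

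**Step 3: the other planning assumption.** With the observed SDs and 62 per arm, power is 72.5% if the true difference is 0.25, 85.3% if it is 0.1 and 91.1% if it is 0.

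**The case against.** The strongest reply is that nothing is hidden or misstated. Section 6 prints the observed SDs, the size of the cut, the reason and the resulting SDs, and 62 and 132 follow from them. That stands: this is a disclosed planning choice, not an error or a contradiction.

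The reason also has some substance. A reader might infer that eligibility is too broad to narrow the spread, since three types of gastrectomy, ages 20 to 80 and ASA up to 3 are admitted. The document does not support that. The exclusion criteria in section 8 also remove patients on anticoagulants, with contraindications to EDA, with abnormal spinal anatomy, after neoadjuvant chemotherapy, with immunodeficiency, and with palliative or emergency surgery. The make-up of the retrospective series is not given, so neither a 10% reduction nor a zero reduction can be shown. This is why the range is the right thing to report.

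A third reply is that the plan was cautious elsewhere. It built in an unfavourable difference of 0.25 from non-randomised groups, where many plans assume equality. That is fair, and step 3 shows how much it matters. It does not remove the point, because section 6 claims its power at that 0.25.

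A reader might also combine the observed SDs with one-sided 2.5% and conclude that power is only 61%. That figure mixes two changes. The Protocol does not state one-sided 2.5%, and moving to it with the planning SDs unchanged already lowers power to 70.1%. Sidedness is a separate matter and the 61% does not measure the SD cut.

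**Conclusion.** The concern holds as a minor one. Power of 80% at 62 per arm depends entirely on the full 10% SD reduction, for whose size the document offers no data. At one-sided 5%, difference 0.25 and margin 1, power lies between 72.5% (no reduction) and 80.2% (full reduction) with 62 evaluable per arm. If all 66 per arm are evaluable, the range is 74.9% to 82.3%. Put differently, the risk of failing to show non-inferiority when the assumed difference is true is about 27% instead of about 20% if the SDs do not shrink.

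This does not show that the trial is underpowered outright. That would require knowing that the SDs will not shrink and that the true difference is as large as 0.25, and the document establishes neither. The validity of a positive non-inferiority conclusion is not touched.

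**What to change.** 1. In section 6, state the power as conditional, for example: *80% power if the SDs are 1.71/1.62; about 76% if they shrink by 5%; about 73% at the observed 1.9/1.8 (one-sided 5%)*.
2. In section 5, replace the unadjusted t-test for the primary endpoint by a linear model with treatment and the allocation strata of section 2. Take the estimated difference and its confidence limit from that model. If the strata are related to pain, this recovers some precision. The amount cannot be quantified from the document, because the strata are not named; they must be named for the model to be specified.

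The cost is a less favourable stated power and a slightly more complex primary model. No increase in enrolment is needed.
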